## Abstract

Introduction and aim: Generalized anxiety disorder (GAD) is a prevalent mental health condition characterized by excessive, often uncontrollable anxiety, frequently accompanied by autonomic dysfunction symptoms. The gut-microbiota-brain axis is implicated in its pathogenesis. Traditional Chinese medicine therapies, including abdominal massage, are increasingly being considered for GAD treatment. This study is designed to evaluate the therapeutic potential of abdominal massage for GAD and its influence on patients' gut microbiota.

Materials and methods: A prospective, assessor-blinded, single-center randomized controlled trial involving 70 GAD patients, randomly allocated to either a combined abdominal massage and medication group or a medication-only group will be conducted. An additional 35 healthy individuals will serve as normal controls.

Results: The primary outcome measure will be the Hamilton Anxiety Rating Scale (HAMA) score pre- and post-treatment. Participants will undergo electroencephalogram (EEG) assessments and provide stool samples for gut microbiota evaluation. Differences between GAD patients and healthy controls will be compared, and changes in the two GAD groups pre- and post-treatment will be monitored. Subsequently, the correlation between EEG findings, gut microbiota, and clinical efficacy in GAD patients will be analyzed.

Conclusion: This study seeks to confirm the therapeutic benefits of abdominal massage for GAD and offer preliminary insights into its underlying mechanisms. Changes in these indicators before and after treatment in both the treatment and control groups will be examined to clarify the potential mechanisms by which abdominal massage may benefit GAD patients. Abdominal massage is hypothesized to alleviate clinical symptoms in GAD patients by modulating the gut-brain axis. If our hypothesis is validated, abdominal massage could emerge as a new alternative treatment for GAD and offer fresh insights into the mechanisms underlying massage therapy. The study's findings will be disseminated through peer-reviewed publications.

## Introduction

Generalized anxiety disorder (GAD) is a mental health condition primarily typified by excessive anxiety, frequently accompanied by symptoms of autonomic nervous system dysfunction [1]. The global lifetime prevalence of GAD is estimated at 3.7% [2]. In China, anxiety disorders' prevalence stands at 5.0%, with a lifetime prevalence reaching up to 7.6%, making it one of the most common mental health conditions [3]. GAD not only undermines the physical and mental health of the affected individuals but also leads to significant social and occupational dysfunction, posing a severe impact on societal and global health [4]. It is the most prevalent type of anxiety disorder [5], with symptoms primarily manifesting as tension, worry, fear, and autonomic dysfunction [6].

At present, the first-line treatment for GAD consists of pharmacotherapy, including benzodiazepine anxiolytics, receptor blockers, and selective serotonin reuptake inhibitors (SSRIs), among others [7]. However, the long-term use of these medications can result in dependence, addiction, an increased incidence of adverse drug reactions, and potential drug resistance, thereby diminishing treatment effectiveness [8]. Moreover, some patients may find the side effects of these medications intolerable and may opt to discontinue treatment. Consequently, there is a pressing need in clinical practice for a safe, effective, and easily applicable treatment method for GAD.

In recent years, the use of Traditional Chinese medicine (TCM) therapies in GAD management has been gaining traction. Particularly, TCM massage, and more specifically abdominal massage, is highly favored by patients due to its capacity to regulate internal organs, promote qi circulation, and balance yin and yang, all while being safe and comfortable [9,10]. Thus, understanding the mechanisms of abdominal massage and other unique TCM therapies has emerged as a significant area of academic interest and a crucial factor in advancing the application and development of TCM.

Objectives

This study aims to evaluate the therapeutic efficacy of abdominal massage in conjunction with escitalopram for the treatment of GAD. By correlating EEG metrics with anxiety assessment scales, a quantitative relationship between symptom scores and objective examination measures is aimed to be established. This will provide auxiliary diagnostic criteria and objective metrics for evaluating clinical efficacy in GAD.

Leveraging fecal 16S rDNA gene sequencing technology, this study will probe into the diversity, richness, and community structure of gut microbiota in GAD patients at a micro level. The regulatory effects of abdominal massage on gut microbiota will also be examined. This will further illuminate the gut-brain interaction mechanisms under the microbiota-gut-brain axis (MGBA) theory, demonstrating how abdominal massage contributes to the improvement of GAD.

## Materials and methods

Study design and setting

This study will be conducted as a parallel-designed, prospective, assessor-blinded, single-center randomized controlled trial. The timeline of this protocol study is from August 2024 to May 2025. This study will take place at the Department of Tui Na and the Psychosomatic Medicine Outpatient Department of the First Teaching Hospital of Tianjin University of Traditional Chinese Medicine, China. Seventy GAD patients will be randomly allocated to either the combined abdominal massage and medication group or the medication-only group. The study will involve various scale assessments, EEG examinations, and stool sample collections both pre- and post-intervention. Additionally, 35 healthy participants will be recruited to serve as normal controls and will undergo relevant tests and examinations upon enrollment. The trial flowchart is depicted in Figure 1, and the study timeline is outlined in Figure 2.

**Figure 1 FIG1:**
[figure not shown]
Flow diagram of the study participants enrollment and follow-up. EEG: electroencephalogram; GAD: generalized anxiety disorder

**Figure 2 FIG2:**
[figure not shown]
Schedule of enrollment, intervention, and assessments of this protocol. In the cells, "X" indicates that the examination was conducted at this time point; an empty cell signifies that the examination was not conducted at this time point. Cells connected by two triangles represent that treatment was administered during this period. HAMA: Hamilton Anxiety Scale; HAMD: Hamilton Depression Scale; SCL-90: Symptom Checklist 90; EEG: electroencephalogram

This randomized clinical trial is aligned with the principles of the Declaration of Helsinki. It has received approval from the Ethics Committee of the First Teaching Hospital of Tianjin University of Traditional Chinese Medicine (TYLL2024[Z]041) and has been registered on the International Traditional Medicine Clinical Trials Registry Platform (ITMCTR2024000140). All participants in this study will be voluntary participants and will sign informed consent forms prior to the commencement of the trial.

Participants

Diagnostic Criteria

The diagnostic criteria for Western medicine in this study are based on the International Classification of Diseases-11 (ICD-11) [11] and the Diagnostic and Statistical Manual of Mental Disorders-5 (DSM-5) [12]. The TCM diagnostic criteria draw on the 2008 Guidelines for the Diagnosis and Treatment of Common Diseases in Internal Medicine (TCM disease diagnosis section) [13] for depression (Appendix A).

Inclusion Criteria for GAD Patients

Participants must meet the previously mentioned Western and Traditional Chinese Medicine diagnostic criteria for GAD. They should be aged between 18 and 65 years, regardless of gender, with a HAMA score ranging from 14 to 29 prior to the trial, indicating mild to moderate GAD. Additionally, they must not have taken any other anti-anxiety or psychiatric medications in the past month and must voluntarily sign an informed consent form.

Exclusion Criteria for GAD Patients

Participants will be excluded if they have anxiety states induced by physical conditions such as hypertension, Sjögren's syndrome, hyperthyroidism, or coronary heart disease. Additionally, individuals currently taking medications that may cause anxiety or those experiencing withdrawal symptoms from long-term use of anti-anxiety medications will be excluded. Anxiety states linked to other mental disorders will also be grounds for exclusion. Patients with severe liver or kidney dysfunction who cannot adhere to the medication regimen, as well as those known to be allergic to any components used in this study, will not be eligible. Furthermore, pregnant or breastfeeding women will be excluded from participation.

Inclusion Criteria for Healthy Participants

Participants must be between 18 and 65 years old, regardless of gender, and should be right-handed. They must be in good health, without any physical discomfort in the past month. Individuals who have undergone central nervous system stimulation, such as repetitive transcranial magnetic stimulation (rTMS), transcranial direct current stimulation (tDCS), or peripheral nervous system stimulation, such as acupuncture or electroacupuncture, will be excluded. Additionally, candidates must have no history of illegal drug use or alcohol abuse. All participants must voluntarily sign the informed consent form and agree to take part in the survey.

Randomization and Assessor-Blinding

Patients with GAD will be randomly assigned to either the treatment group or the control group using computer-generated random numbers. The random sequences, identified with unique labels, will be sealed in opaque envelopes, which will only be opened upon the enrollment of a participant. The sequence generation and allocation will be carried out by independent personnel who are not involved in the trial. Healthy participants will be enrolled as normal controls, without undergoing randomization.

Blinded assessments will be performed, with patients receiving treatment in distinct settings. Efficacy will be evaluated by a third party who is not privy to the group assignments. During data aggregation, blinded statistical analysis will be conducted. Throughout the study, researchers, clinical operators, efficacy evaluators, and data statisticians will maintain separation to ensure the integrity of the blinding process.

Sample Size

Based on prior research, the Hamilton Anxiety Rating Scale (HAMA) score for the medication group was 18.61±3.17 [14]. The HAMA score for the treatment group is anticipated to decrease by 2.76 points. With a two-sided significance level (α) of 0.05 and a power of 90%, the required sample size was calculated using PASS 2021 software. This resulted in a needed sample size of N1=29 for the treatment group and N2=29 for the control group. Taking into account a potential dropout rate of 20%, a minimum of 35 subjects per group is needed, amounting to a total of at least 70 subjects. In addition, 35 healthy participants will be included in the study.

Intervention

Treatment Group GAD Patients

The medication regimen for this study will consist of oral escitalopram (Bailex) (Sichuan Kelun Pharmaceutical Co., Ltd., China; approval no.: National Drug Standard H20080788; specification: 10 mg × 10 tablets) [15]. Each participant will take 10 mg once daily at 09:00 AM for a duration of eight weeks.

In addition to the medication, participants in the treatment group will receive abdominal massages. The massage procedure will follow guidelines from the "Tui Na" textbook [16] edited by Fang Min and Wang Jingui (5th edition, "14th Five-Year Plan" for higher education in TCM). Participants will lie in a supine position while the practitioner performs rhythmic circular motions on the abdomen with the palm, 5 minutes clockwise and 5 minutes counterclockwise, at a frequency of 120 times/min. This is followed by finger massage on Zhongwan, Tianshu, Qihai, and Guanyuan points for 5 minutes at a frequency of 160 times/min. The total treatment time is approximately 15 minutes, conducted once daily, five days a week, for eight weeks.

To ensure the quality of the abdominal massage and the precise location of the acupoints, several measures will be implemented. Prior to the trial, [name] massage techniques, including force and frequency, will be calibrated using the YF-3 Hand Technique Measurement Instrument to create a standardized model. During the trial, experienced physicians with over 10 years of clinical practice will carry out the procedures. Additionally, all operators will receive training to ensure their techniques align with the model established by the YF-3 instrument.

After GAD patients are enrolled, they will initially receive two weeks of abdominal massage treatment by a Tui Na doctor, followed by training in the technique. After two weeks, the force applied by patients during self-massage will be measured to standardize the technique. For the remaining six weeks, patients will visit the clinic once a week for treatment, with the remaining sessions performed at home. Patients will receive a video tutorial on abdominal massage and are required to upload videos and photos of their self-treatment for review. If inconsistencies are found, the doctor will provide online guidance. If the technique is corrected after three attempts, the patient will remain in the study; otherwise, they will be considered a dropout.

The acupoints utilized in this study are defined according to the 2021 national standard (GB/T12346-2021) titled "Names and Locations of Acupoints."[17] These acupoints include Zhongwan (CV12), which is situated in the upper abdomen, 4 cun above the navel along the anterior midline; Tianshu (ST25), located at the level of the navel, 2 cun lateral to the anterior midline; Qihai (RN6), found in the lower abdomen, 1.5 cun below the navel on the anterior midline; and Guanyuan (CV4), positioned 3 cun below the navel on the anterior midline. A map illustrating the locations of these acupoints is provided in Figure 3.

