**Figure 3 FIG3:**
[figure not shown]
Acupoint location diagram.

Control Group GAD Patients

Medication includes oral escitalopram (Bailex) (Sichuan Kelun Pharmaceutical Co., Ltd., China; approval no.: National Drug Standard H20080788; specification: 10 mg × 10 tablets), 10 mg once daily at 09:00 AM for eight weeks.

Healthy Participants

Healthy participants will not receive any treatment. They will be screened based on their medical history and HAMA scores. General information and HAMA scores will be recorded. Upon enrollment, EEG and stool samples will be collected from healthy participants.

Statistical analysis

This study will conduct statistical analysis based on the principle of intention-to-treat (ITT), including all patients who entered randomization and were not excluded in the statistical analysis. The efficacy endpoints will be analyzed using the full analysis set (FAS), supplemented by the per-protocol set (PP). Safety endpoints will be analyzed using the safety set (SS).

IBM SPSS Statistics for Windows, Version 26 (Released 2019; IBM Corp., Armonk, New York, United States) will be used for statistical processing. Measurement data will first be tested for normal distribution and homogeneity of variance. Data that meet the normal distribution and homogeneity of variance will be statistically described using the mean ± standard deviation (x̄±s), and data that do not meet the normal distribution and homogeneity of variance will be statistically described using the median (M) and the 25th and 75th percentiles (P_25_, P_75_).

For the comparison of measurement data between two groups, a paired two-sample t-test will be used for data that meet the normal distribution, and a rank-sum test will be used for data that do not meet the normal distribution. For the comparison of data at different time points after treatment with pre-treatment data, a paired t-test will be used for data that meet the normal distribution, and a rank-sum test will be used for data that do not meet the normal distribution. For the comparison of measurement data among multiple groups, a one-way ANOVA will be used for data that meet the normal distribution, and a rank-sum test will be used for data that do not meet the normal distribution.

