## Conclusions

This is the first randomized controlled trial to incorporate abdominal massage into the gut-brain axis framework for GAD patients. EEG and gut microbiota are indicators of gut-brain axis function. Differences in these indicators between GAD patients and healthy individuals will be identified to determine the characteristics of gut-brain interactions in GAD patients. Furthermore, changes in these indicators before and after treatment in the treatment group and the control group will be studied to elucidate the potential mechanisms of abdominal massage in treating GAD patients. The main advantage of this study is the collection and evaluation of multifaceted data. Abdominal massage is hypothesized to improve clinical symptoms in GAD patients by regulating the gut-brain axis. If this hypothesis is confirmed, abdominal massage will not only become a new alternative method for treating GAD but also provide new insights into the mechanisms of massage therapy.

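### The GAD-versus-healthy comparison of EEG and microbiota is open to confounding: several non-disease criteria bind healthy controls only, and every stated test is covariate-free

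*Protocol article*

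**What the plan says.** **Healthy controls.** Under Inclusion Criteria for Healthy Participants: "Participants must be between 18 and 65 years old, regardless of gender, and should be right-handed". A further health rule reads "They must be in good health, without any physical discomfort in the past month". Excluded are "Individuals who have undergone central nervous system stimulation, such as repetitive transcranial magnetic stimulation (rTMS), transcranial direct current stimulation (tDCS), or peripheral nervous system stimulation", with acupuncture and electroacupuncture given as examples of the last. Finally, "candidates must have no history of illegal drug use or alcohol abuse".

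**Patients.** Under Inclusion Criteria for GAD Patients: "They should be aged between 18 and 65 years, regardless of gender, with a HAMA score ranging from 14 to 29 prior to the trial". Patients must also meet the Western and TCM diagnostic criteria in Appendix A and must have taken no other psychiatric medication in the past month. The exclusions cover anxiety due to physical disease, to medication or its withdrawal, or to another mental disorder, together with severe liver or kidney dysfunction, allergy, pregnancy and breastfeeding. Handedness, prior stimulation or acupuncture, and a general history of alcohol or drug abuse are not mentioned.

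**Analysis.** The Statistical analysis section gives t-tests, rank-sum tests, repeated-measures ANOVA, the Friedman test and χ² tests. For more than two groups: "For the comparison of measurement data among multiple groups, a one-way ANOVA will be used", with a rank-sum test as the non-normal alternative. No model with covariates appears.

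**Use of the comparison.** The Conclusions state: "Differences in these indicators between GAD patients and healthy individuals will be identified to determine the characteristics of gut-brain interactions in GAD patients". The Objectives also expect EEG to supply auxiliary diagnostic criteria.

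**The concern.** The healthy group is not randomised, so a difference from patients can reflect GAD or anything else that separates the groups. By restricting controls on handedness, prior stimulation or acupuncture, and substance use, the plan treats these factors as relevant to selection, but it restricts them on one side only. The stated tests would not remove a resulting difference, or one due to age or sex, which can vary widely within 18 to 65 and either sex.

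At stake is the interpretation of the healthy reference. A gap produced by selection could be reported as a feature of GAD and then used to judge whether treatment moves patients towards normal. The limitations in the Discussion name blinding, the fixed massage protocol and the small sample, but not the comparability of the healthy group.

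**Working it through.** **1. The plan's own figure.** The article gives no calculation for the patient-versus-healthy comparison. Its only sample-size figure, 29 per randomised arm (HAMA difference 2.76, SD 3.17, two-sided 5%, power 90%), reproduces: an exact two-sample t-test gives 28.7, rounded up to 29. It has no bearing on this point.

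**2. Criteria side by side.**

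| Factor | Healthy controls | GAD patients |
|---|---|---|
| Age, sex | 18–65, either sex | 18–65, either sex |
| Handedness | right-handed only | no rule |
| Prior brain stimulation, acupuncture | excluded | no rule |
| Drug or alcohol abuse | no history allowed | only anxiety attributable to a substance or its withdrawal |
| Physical health | no discomfort for one month | organic disease excluded (Appendix A, exclusion criteria) |
| Pregnancy, breastfeeding | no rule | excluded |

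Rows two to four are healthy-only rules on non-disease factors. The physical-health row is partly covered for patients and partly a consequence of the disease, so it is not counted here.

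**3. Size, with the outcome shift assumed.** Suppose GAD has no effect on a measure, but non-disease differences shift its mean by s SD between patients and controls. The documents do not give s, so a range is used.

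- Three-group ANOVA, 35/35/35: noncentrality λ = 35 × s² × 2/3; reject if F(2, 102) > 3.09.
- Two-sample t-test, 70 against 35: SE = √(1/70 + 1/35) = 0.207 SD; noncentrality s/0.207, 103 df.
- Two-sample t-test, 35 against 35: SE = √(2/35) = 0.239 SD. This is included because the Gut Microbiota Monitoring section takes stool only from randomly selected patients, so fewer than 70 may contribute.

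| s (assumed) | λ | ANOVA 35/35/35 | t, 70 vs 35 | t, 35 vs 35 |
|---|---|---|---|---|
| 0.20 | 0.93 | 12% | 16% | 13% |
| 0.30 | 2.10 | 23% | 30% | 24% |
| 0.45 | 4.73 | 47% | 58% | 46% |

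The nominal rate is 5% throughout.

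**4. What produces such a shift.** For one continuous covariate, s = r × d, where d is its imbalance in SD and r its correlation with the outcome (both assumed).

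| d | r | s | ANOVA 35/35/35 |
|---|---|---|---|
| 0.25 | 0.2 | 0.05 | 5.4% |
| 0.5 | 0.3 | 0.15 | 9.0% |
| 0.5 | 0.5 | 0.25 | 17.1% |
| 0.8 | 0.5 | 0.40 | 38.1% |

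A shift of 0.45 SD from one covariate needs d = 0.45/0.5 = 0.9 at r = 0.5, or 0.45/0.3 = 1.5 at r = 0.3. The top of the range in step 3 is therefore demanding for a single factor. For a yes/no factor such as handedness, s is the share of patients who would fail the rule times the factor's effect, so a rule that few patients would fail contributes little.

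**5. Does adjustment help?** In 4,000 simulated trials per setting with no disease effect, the unadjusted three-group ANOVA rejected in 8.4%, 16.3% and 38.6% for (d, r) = (0.5, 0.3), (0.5, 0.5) and (0.8, 0.5). A pooled 70-against-35 linear model including the covariate rejected in 4.6%, 5.5% and 5.1%.

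**The case against.** Four objections carry weight.

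- **Patients do face health and substance rules.** Appendix A requires normal physical and laboratory examinations and rules out substance or medical causes, and recent psychiatric medication is barred. A reader might infer that none of the healthy-group restrictions has a patient counterpart; that is not so. What remains is handedness, prior stimulation or acupuncture, and the broader drug and alcohol history.
- **Freedom from physical discomfort cannot be asked of patients.** Fatigue, muscle tension, sleep disturbance and chest or rib pain are among the diagnostic features. Restricting patients to the full healthy-group list would leave few or none.
- **The article is condensed.** A reader might infer that controls are unmatched. The article is merely silent, and matching or a covariate list may stand in the full protocol or analysis plan. The unequal criteria and the covariate-free tests, however, are stated.
- **The ANOVA sentence does not name the healthy group.** A reader might infer that the plan splits patients into two arms for the baseline comparison with healthy controls. Two patient arms plus healthy controls is the only three-group structure in the trial, but the Abstract and Conclusions speak of GAD patients as one group against healthy individuals, and two-group tests are also listed. A fault of splitting is not established. It makes no difference here, because the two-group tests carry no covariates either.

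It is also fair to say that the healthy group plays no part in the arm-against-arm comparisons, and that the Abstract promises only preliminary insight into mechanisms.

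**Conclusion.** The point holds as a vulnerability, not as a demonstrated bias. Three healthy-only, non-disease criteria and a covariate-free test list leave the patient-versus-healthy EEG and microbiota comparison open to confounding, while the Conclusions give it a determining role. To say that the results would be confounded goes further than the documents allow, since they give no imbalance in any factor.

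The size is unknown. It runs from negligible (5.4% against 5% at a 0.05 SD shift) to about 12–47% under the three-group ANOVA for assumed shifts of 0.2–0.45 SD. Those rates assume complete data on 35 per group, normal outcomes and no true disease effect.

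The randomised HAMA comparison, and any randomised comparison of EEG or microbiota between the two arms, is unaffected. The change is worth making because it is cheap and because a factor not recorded at enrolment may not be recoverable later. It does not threaten the trial's main efficacy result.

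**What to change.** 1. **Baseline contrast.** Compare baseline EEG and microbiota measures in one contrast, pooled GAD patients with data against healthy controls, using a linear model adjusted for age and sex. Keep the randomised-arm comparisons separate.
2. **Recording.** Record handedness, prior brain stimulation or acupuncture, and alcohol or drug use in both groups.
3. **Sensitivity analysis.** Repeat the contrast in patients who meet those three non-disease criteria, leaving out the rule on physical discomfort. Restriction suits handedness better than adjustment, because the control group will contain no left-handers.
4. **Matching.** Frequency-match controls to patients on age band and sex, if the full protocol does not already do so.
5. **Wording.** Describe the result as an association with GAD rather than as determining its characteristics, and list the comparability of the healthy group among the limitations.

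Cost: a few case-report-form items, a simple covariate model and somewhat slower recruitment of controls. No extra participants or procedures are needed. Items 2 and 4 must be settled before controls are enrolled.

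### A 20% loss from 35 per group leaves 28, one short of the 29 the plan says it needs; the effect on power is minor

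*Protocol article*

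**What the plan says.** All the figures are in the Sample Size section of the protocol article:

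- Prior result: "the Hamilton Anxiety Rating Scale (HAMA) score for the medication group was 18.61±3.17".
- Anticipated effect: "The HAMA score for the treatment group is anticipated to decrease by 2.76 points".
- Error rates: "With a two-sided significance level (α) of 0.05 and a power of 90" per cent.
- Evaluable number: "This resulted in a needed sample size of N1=29 for the treatment group and N2=29 for the control group".
- Dropout allowance: "Taking into account a potential dropout rate of 20%, a minimum of 35 subjects per group is needed".
- Resulting enrolment: no fewer than 70 patients across the two groups.

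The formula behind the allowance is not printed. The Abstract and the Study design and setting section repeat the 70 patients. No other section gives a different dropout rate or another inflation rule.

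**The concern.** A dropout rate is ordinarily a fraction of those enrolled. To end with 29 evaluable patients after a 20% loss, 29 must be divided by the retained fraction, 0.80. The printed 35 is smaller than that result and equals what one gets by adding 20% to 29. Taken together, 35 enrolled, 20% lost and 29 needed cannot all be true.

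At stake is the accuracy of the planning statement. The article calls 35 a minimum and ties it to 90% power, and all the inputs needed to check it are printed, so a reader who does the sum will find that it fails.

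**Working it through.** **Inputs**, all from the Sample Size section: difference δ = 2.76, SD σ = 3.17, two-sided α = 0.05, power 90%, 29 evaluable per group, dropout 20%, 35 enrolled per group. Two readings are needed to use them. The 2.76 is taken as the between-group difference, and 3.17 as an SD common to both groups, because no separate SD is given for the treatment group.

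**Step 1: reproduce 29.**

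Normal approximation: n = 2 × (1.960 + 1.2816)² × (3.17/2.76)² = 27.72, so 28 per group.

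Two-sample t-test: noncentrality = δ / (σ × √(2/n)), with 2n − 2 degrees of freedom.

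| n per group | Power, t-test | Power, normal approximation |
|---|---|---|
| 28 | 89.2% | 90.3% |
| 29 | 90.3% | 91.2% |
| 35 | 94.8% | 95.4% |

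The t-test calculation first reaches 90% at n = 29, which matches the plan exactly. A one-sided test (normal approximation) would need 23 and does not match. The base figure is therefore sound, and the fault lies only in the step that follows.

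**Step 2: apply the dropout rate.**

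- Dividing by the retained fraction: 29 / (1 − 0.20) = 36.25, so 37 per group and 74 in total.
- Adding 20%: 29 × 1.20 = 34.8, so 35 per group and 70 in total. This matches the printed figures.

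**Step 3: check 35 directly.** This does not depend on how 35 was obtained.

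- Evaluable at 20% dropout: 35 × 0.80 = 28, which is below 29.
- Largest dropout that still leaves 29: 1 − 29/35 = 17.1%, or 6 of 35 patients.

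**Step 4: cost in power at 20% dropout, with every dropout lost to the analysis.**

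- Exactly 28 per group: 89.2%, which is 0.8 points under the target.
- If the number of completers in each group varies as Binomial(35, 0.8): expected power about 89.0%.
- With 37 enrolled and completers varying in the same way: about 90.6%.

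**The case against.** The strongest reply is that nothing of consequence follows. The gap is one evaluable patient per group and less than one point of power. With 28 per group the t-test calculation returns to about 90% if the difference is 2.80 instead of 2.76, or the SD 3.13 instead of 3.17. Planning inputs taken from a single prior study are unlikely to be known that closely. This stands, and it fixes the size of the point.

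A second reply is that 28/0.80 is exactly 35 and that the normal approximation gives 28. So a correct inflation from 28 also leads to 35. This shows that the 29 × 1.2 route cannot be asserted as fact. It does not repair the text, which states 29, and the method that yields 29 gives 89.2% at 28.

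A third reply is that patients counted as dropouts may still be analysed. The Statistical analysis section follows intention-to-treat and uses the full analysis set for efficacy. The Intervention section also classes as dropouts those patients whose self-massage technique stays uncorrected, and they could still have a HAMA score. If all 35 per group were analysed, power would be 94.8%. This softens the power figure. It does not make 35 the right allowance for 20%, because the Sample Size section itself treats dropouts as needing replacement.

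The words for a minimum and for at least 70 might be read as leaving room for more patients. That helps little, since the Abstract and the Study design and setting section both give 70.

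**Conclusion.** The point holds as an inconsistency between printed figures: 35 per group with 20% dropout gives 28, not 29. The minimum that fits the stated inputs is 37 per group, 74 in total, which is four more patients than planned. It is a minor error. Power is about 89.2% instead of 90%, assuming that dropout is a fraction of those enrolled, that every dropout is lost to the analysis, and that the t-test calculation reproducing 29 is the one used.

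A reader might infer three stronger things that the documents do not support:

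- That the authors multiplied 29 by 1.2. The figure is consistent with this, but no formula is shown.
- That the trial is underpowered in any material sense. The shortfall is under one point, and it may not arise at all if dropouts contribute outcomes to the full analysis set.
- That reproducing 29 shows 2.76 and 3.17 to be end-of-treatment values. The calculation uses only a difference and a common SD; the visit does not enter it. The section does not date the prior 18.61 ± 3.17.

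**What to change.** Keep enrolment at 35 per group and correct the statement in the Sample Size section, for example: *With 35 patients per group, 29 evaluable patients per group (90% power) are retained if dropout does not exceed about 17%; with 20% dropout, leaving 28 per group, power is about 89%.*

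The same passage should say that 2.76 is the assumed between-group difference in HAMA score and 3.17 the common SD, since the calculation reproduces on that reading and the present wording could be taken as a within-group fall. No visit should be attached to these values unless the sponsor can confirm it from the cited source.

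The cost is a sentence or two and a slightly less favourable dropout or power figure. The alternative is to keep both 20% and 90% and enrol 37 per group (74 in total), at the cost of four more patients and a matching change wherever 70 appears. Given the size of the discrepancy, restating the figures is enough.
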